## Methods

### Overall study design

We will run a quasi-experimental trial of a complex multifactorial intervention.^23^ Using a before and after study design, we will pilot the Outreach service to patients with AKI. Patients will be recruited once they have an electronic alert indicating that they have AKI. Inclusion and exclusion criteria will then be applied (box 1). There will be no patient-level randomisation to avoid the risk of contamination, as this is a pilot for a CRT. The study has been approved by (1) the National Research Ethics Service (Reference: 14/EM/0184, NRES Committee East Midlands—Nottingham 1, approved 22 May 2014) and (2) the Confidentiality Advisory Group (CAG Reference: CAG 2-07(a)/2014—approved 30 May 2014).
Box 1Inclusion and exclusion criteria for the Acute Kidney Outreach to Reduce Deterioration and Death (AKORDD) studyInclusion criteria:Adult (≥18 years) patients with an alert due to AKI from a blood test arising from Heartlands or Good Hope Hospitals (and their associated postcodes for outpatients/primary care).AKI stage 1, 2 or 3.Exclusion criteria:Patient deceased at the time of Outreach team intervention.Patient already accepted for dialysis by HEFT renal unit.Known dialysis/end-stage renal disease patients (excluded from alerts).Other patients with stable chronic kidney disease (definition of stable CKD), or progressive CKD where there is no obvious change in the rate of progression of the CKD (ie, no acute deterioration, just steady progression).Patients with CKD and stage 1 AKI based on an absolute creatinine rise of ≥26 µmol/L but who have a relative rise of ≤15% in creatinine are regarded as stable CKD and therefore not eligible for the study.Children or young people <18 years of age.Patients in the terminal phase of malignancy or end-stage major organ disease where they have little potential to benefit from Outreach. These would typically be identified as having a life expectancy likely to be <3 months.Patients lacking mental capacity (unless enrolment agreed in writing with a personal consultee or nominated consultee (after phase) or personal consultee (before phase)).Other technical aspects of making alert not credible: inadequate data; suppressed creatinine at baseline.

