It was impractical to take written informed consent from the large numbers of patients involved over two hospitals, when the study was focused on providing AKI Outreach to clinicians. Therefore, it was agreed with the research ethics committee that we would write to all enrolled patients giving them an ‘opportunity to dissent’ or ‘opt out’ of the study. The opt out letter will be sent to the patient's home address as soon as possible after enrolment. In conjunction with the opt out letter, a leaflet explaining AKI will be sent to patients in the intervention group only.

The study is registered at ClinicalTrials.gov (NCT02398682). It is funded by the Research for Patient Benefit programme of the UK National Institute for Healthcare Research (PB-PG-1111-26038) and sponsored by the Heart of England Foundation Trust. The trial has two phases and four groups (2 during each phase—see also figure 1):
The before phaseDuring the 2-month before phase, patients in the two groups will be observed for the outcome measures, without any intervention, thus defining outcomes with good standard care. There will be two before phase groups:
Heartlands and area patients—patients with AKI in secondary and primary care—observed only.Good Hope and area patients—patients with AKI in secondary and primary care—observed only.The after phaseDuring the 5-month after phase, the intervention will be delivered to the intervention group (Heartlands and area) only. There will be two after phase groups:Heartlands hospital and area patients—intervention provided for patients with AKI in secondary and primary care, mainly using Outreach via telephone (see below).Good Hope hospital and area patients—patients with AKI in secondary and primary care—observed only.

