### Study team

The AKI Outreach team will function during working hours, 5 days/week. The ideal service, addressing AKI 7 days a week, is beyond the resources of this pilot. The model is a mixed skills team, allocating tasks using an electronic list of alerts and the electronic study database. The core Outreach team consists of an experienced renal consultant (usually the Chief Investigator), renal research fellow (working at junior specialist registrar level) and a critical care research (trained in AKI care) nurse. The core clinical team members will be primarily responsible for delivering the interventions, in the form of telephone consultation, with or without a ward visit, triggered by the AKI alert. The core team members are supported by other research staff, who help with the research data collection. Each working day patients are prioritised according to AKI severity.

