### Intervention package

The Outreach team will advise on an evidence-based package of care (these interventions are limited to the intervention arm):
*Diagnostic and monitoring recommendations*—to rapidly establish a credible diagnosis of the cause of AKI including:
Improved assessment of volume status;Standardised use of urine dipstick (often missed);Appropriate sepsis investigations;Urgent ultrasound with suspected obstruction, while avoiding early ultrasound in patients at low risk of obstruction.*AKI treatment recommendations*—to treat correctable causes of AKI:
Rapid, limited treatment of hypovolaemia, with avoidance of iatrogenic fluid overload, recently recognised as a significant cause of mortality in AKI;Rapid sepsis therapy;Cessation of potentially nephrotoxic agents (many well known, such as ACE inhibitors and non-steroidal drugs, but others less well known such as Aciclovir);Urgent relief of urinary tract obstruction.*Recommendations to manage the acute illness:*
Where needed, recommendations will be made to address key aspects of the major underlying comorbidity;Improve nutrition, as malnutrition is known to be associated with poor outcome. Dietetic referral will be made for all appropriate inpatients with stage 3 AKI.*Pathway recommendations:*
For inpatients, refer to the Renal and/or Critical Care Outreach teams, as appropriate;For patients in the community, arrange urgent or immediate outpatient review or admission, as appropriate;Arrange formal palliative care when necessary.*Stage-based AKI management:*
Stage 1 patients will typically receive a single intervention call;Stage 2 patients will usually receive a single intervention call and be discussed with the renal consultant;Stage 3 inpatients will be reviewed by a consultant, ideally within 24 hours of the AKI Outreach team being aware of their presence in the intervention hospital (Heartlands Hospital);Rapid AKI follow-up clinic—we will offer surviving patients with stage 3 AKI a rapid follow-up clinic appointment, ideally within 7 days of discharge, or within 7 days of the alert if the patient is not admitted to hospital.

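### The poor-prognosis exclusion is discretionary and not closed before the Outreach call, which leaves room for fuller screening-out of high-risk patients in the Heartlands after-phase group

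*Protocol article*

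**What the plan says.** Under Overall study design, patients are identified by an electronic alert, and "Inclusion and exclusion criteria will then be applied (box 1"). Box 1 excludes "Patients in the terminal phase of malignancy or end-stage major organ disease where they have little potential to benefit from Outreach" and adds "These would typically be identified as having a life expectancy likely to be <3 months". The same box excludes a "Patient deceased at the time of Outreach team intervention".

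Allocation is open: "There will be no patient-level randomisation to avoid the risk of contamination". The group follows from hospital area and calendar phase. In the before phase, "patients in the two groups will be observed for the outcome measures, without any intervention"; Good Hope and its area are also only observed in the after phase. Data collection and recruitment has the study team viewing all alerts in a list and moving patients into the study database at enrolment.

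Contact with the treating clinicians, by phone with or without a visit, is confined to the intervention group (Study team; Interventions; Intervention package). One of the recommendations available in that contact is "Arrange formal palliative care when necessary".

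Death from any cause within 30 days is part of the primary composite (Outcomes). Statistical analysis compares before with after separately at each site, uses the control site to look for system-wide change, and says the pilot is not powered for a full before/after comparison.

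**The concern.** The criterion asks for a judgement about benefit from a service that three of the four groups never receive. The three-month anchor narrows the judgement, but it is qualified as typical and likely, and no score or documented marker is required.

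In the Heartlands after phase, the team speaks to the treating clinician and may learn about prognosis. The article gives no cut-off that would stop such information from feeding back into eligibility. The neighbouring exclusion for patients already dead when Outreach intervenes shows that at least one criterion is judged at contact, so eligibility is not wholly settled at the alert.

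The patients concerned are those most likely to die within 30 days. If more of them were removed from one group, its composite rate would fall with no treatment effect. Good Hope is observed in both phases, so a stable Good Hope rate would not rule out a shift confined to the Heartlands after phase.

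**Working it through.** **Inputs from the protocol article (After phase sample size; Overall study design)**
- Planning composite rate p = 40%.
- Intervention group, after phase: n above 1000, with a stated 95% CI of 37% to 43%.
- Control group, after phase: n = 370, with a stated 95% CI of 35% to 45%.
- Before phase 2 months, after phase 5 months; no before-phase sample size is set.

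**Inputs assumed, because the article gives none**
- x = extra share of otherwise eligible patients excluded in the Heartlands after phase: 2 to 5%.
- r = composite event risk among them: 70 to 80%.
- Heartlands before-phase number: about 400, from 1000 × 2/5; range 300 to 500.

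**Step 1. Reproduce the plan's precision.** Half-width = 1.96 × √(p(1 − p)/n).
- n = 1000: 1.96 × √(0.24/1000) = 3.04 points, giving 36.96% to 43.04%.
- n = 370: 1.96 × √(0.24/370) = 4.99 points, giving 35.01% to 44.99%.

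Both agree with the article.

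**Step 2. Effect of differential exclusion with no treatment effect.** Observed rate p′ = (p − x·r)/(1 − x).

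| x | r | p′ | Fall (points) |
|---|---|---|---|
| 2% | 70% | (0.40 − 0.014)/0.98 = 39.4% | 0.6 |
| 3% | 80% | (0.40 − 0.024)/0.97 = 38.8% | 1.2 |
| 5% | 80% | (0.40 − 0.040)/0.95 = 37.9% | 2.1 |

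**Step 3. Choose the right yardstick.** The 3-point half-width in Step 1 describes one proportion. The comparison exposed here is a difference between two phases, with half-width 1.96 × √(0.24/n_before + 0.24/1000).
- n_before = 300: 6.3 points.
- n_before = 400: 1.96 × √(0.0006 + 0.00024) = 5.7 points.
- n_before = 500: 5.3 points.

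At 400, the illustrated shift is 0.6/5.7 ≈ 11% to 2.1/5.7 ≈ 37% of the half-width.

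**Step 4. Which comparison can show the shift.** Contact with clinicians differs between phases at Heartlands but not at Good Hope. An exclusion shift that depends on contact would therefore appear in the Heartlands before/after contrast only, and there it would look the same as benefit.

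**The case against.** The strongest reply is that the mechanism is not in the text. The article applies the criteria once the alert appears and has patients transferred from the alert list at enrolment, so the natural reading is that screening precedes the call. The criterion is worded identically for all four groups, names disease states and carries a three-month anchor. Listing palliative care among the recommendations implies that some patients found on contact to be near the end of life stay enrolled, which is what the fix asks for. Comorbidity and solid-tumour stage are collected for everyone, so a gross imbalance in malignancy might be seen. Who screens and from what source may well be in the full protocol.

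Much of this stands. A reader might infer that the prognosis judgement is made or revised after the call; no section says so. A reader might also infer that the observed groups are screened from electronic records alone; the article does not state the screening source for any group. The description of the core team ("The core Outreach team consists of an experienced renal consultant (usually the Chief Investigator") concerns who delivers Outreach, not who judges eligibility.

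What remains is the rule as stated. It is discretionary, it is framed by benefit from the intervention, it is applied in an open design, and it has no closing point before contact. That is a feature of the published criterion, not merely operational detail left out of an article.

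**Conclusion.** The point holds as a possible bias that the stated rule leaves open, not as a demonstrated one. The documents establish neither that a differential exists nor its size or direction. The 0.6 to 2.1 point shift rests wholly on the assumed 2 to 5% extra exclusions at 70 to 80% event risk.

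It is tempting to set that shift against the planned 3-point half-width and conclude that the bias could account for an apparent benefit. The documents do not support this: that figure is for a single group's rate. Against the roughly 5 to 6 point half-width of the before/after difference (about 400 before-phase patients assumed), the shift would contribute to an observed difference but would not decide it.

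The feasibility aims are little affected. The article disclaims power for the before/after comparison and says that a full cluster trial is needed for a definitive answer. This is a cheap improvement of minor severity.

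**What to change.** In all four groups, decide the poor-prognosis exclusion only from information in the patient record dated at or before the index alert. Log the decision and its reason before any Outreach contact. Keep in the analysis any enrolled patient later found to be terminal. Report the number excluded for this reason in each of the four groups.

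The cost is a change of wording in Box 1 and one logged screening field. There are two downsides. A few patients unlikely to benefit will stay in the intervention group and slightly dilute any effect. The rule also depends on the quality of documentation, which may differ between the two sites and between primary and secondary care; the counts by group would help to show whether it does.

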### After phase sample size

For the before phase, no sample size is required and eligible patients during the study period will be recruited. The sample size was calculated with the intent of estimating uncertainty of outcomes, to inform the design of the future cluster trial. Our previous work suggested that the combined outcome would be seen in about 40% of patients having an alert. With a sample size of >1000 (intervention group—Heartlands and area, after phase), a 95% CI of width 6% (37% to 43%) can be calculated. A sample size of 370 (control group—Good Hope and area, after phase) will allow us to produce a 95% CI of width 10% (35% to 45%).

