### Statistical analysis

The focus of the study is to assess feasibility of all aspects prior to full-scale evaluation. The data collected in this pilot study will be used to assess the uncertainty of the primary outcome. Further analyses will separately compare the before and after arms at the intervention and control sites. We note that the intervention and control sites cannot be directly compared. The control site data will be used to assess any ‘system-wide’ change in AKI outcomes. Additionally, survival analyses will be carried out, examining time to first composite primary outcome, and Kaplan-Meier survival curves produced for each of the four groups. This pilot study is not powered to provide a full comparison of the before and after phases. Among the end points, the use of dialysis and frequency of non-dialytic AKI complications will give an indication of the safety of the intervention. We will analyse estimated Glomerular Filtration Rate (eGFR) and CKD stage at a group level and changes at individual patient level. We will also explore the potential of using these data to validate our previous prognostic index.^9^

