### Discussion and limitations of the study

The national algorithm for staging of AKI means that identification of patients with AKI is standardised. The ‘opt out’ consent process enables large-scale recruitment. The ethos of AKI Outreach is that advice is offered to the primary clinician, who may choose to act upon or ignore that advice. A key challenge in implementing the intervention is reaching and influencing the decision maker(s) within the primary team, especially as they have varying roles and beliefs.

The AKI Outreach service runs only 40 hours/week and not out-of-hours. As this is a pilot for a full CRT, there were only two sites and randomisation was not undertaken. Inevitably, the intervention and the control sites are different to a certain extent. The latter does not have on-site nephrology services. A full CRT is needed to provide a definitive answer regarding any benefits of this approach. What would a successful pilot look like? The delivery of recommendations acceptable to clinicians, comparable to our previous work (median of 3 within a median of 15 hours), and to large numbers of patients is a key indicator of success. The control group should show no evidence of a system-wide change in before and after AKI outcomes. The intervention group will provide evidence of the feasibility and safety of the intervention.

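### The consultee rule for patients lacking capacity changes between phases, so both within-site before/after contrasts are open to a case-mix bias of unknown size and sign

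*Protocol article*

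**What the plan says.** Box 1 (Protocol article, Overall study design) lists lack of mental capacity as an exclusion, lifted when enrolment is agreed in writing with a "personal consultee or nominated consultee (after phase) or personal consultee (before phase". The rule is written by phase and not by site, so it covers Heartlands and Good Hope alike.

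The Statistical analysis section then states: "Further analyses will separately compare the before and after arms at the intervention and control sites". It rules out the other obvious comparison ("We note that the intervention and control sites cannot be directly compared") and gives the control site a specific task: "The control site data will be used to assess any ‘system-wide’ change in AKI outcomes". The Discussion and limitations section makes the result of that task part of what a successful pilot would look like: "The control group should show no evidence of a system-wide change in before and after AKI outcomes".

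The article does discuss one phase difference in case mix. The Data collection and recruitment section notes that the before phase may take up more patients with recurrent AKI and calls this a potential limitation. The consultee difference is not mentioned there or elsewhere in the article.

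**The concern.** A before/after comparison within a site needs the two cohorts to be drawn from the same kind of patient. Here the entry rule widens at the point where the Heartlands intervention starts. Patients lacking capacity who do have a personal consultee are eligible in both phases. Those who have none are eligible only in the after phase.

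If this added group has a composite risk different from the rest, the after-phase rate moves for a reason unrelated to Outreach. At Heartlands the movement would be mixed into the apparent effect of the intervention. At Good Hope it could imitate or hide a system-wide change, which is what the control site is there to detect. Because the two sites are analysed separately, the plan has no step in which a shift common to both would cancel. The time-to-event curves planned for each of the four groups are exposed in the same way.

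**Working it through.** **1. The plan's own figures.** The After phase sample size section assumes that "the combined outcome would be seen in about 40% of patients having an alert". With the Wald interval, half-width = 1.96 × √(p(1 − p)/n) and p = 0.40:

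- n = 1000 (Heartlands, after): 1.96 × √(0.24/1000) = 3.0 points, so 37.0% to 43.0%. This matches the article's "a 95% CI of width 6% (37% to 43%) can be calculated".
- n = 370 (Good Hope, after): 1.96 × √(0.24/370) = 5.0 points, so 35.0% to 45.0%, again as stated.

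These single-group intervals do not depend on the consultee rule at a given n.

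**2. Shift caused by the change in eligibility.** Let a be the share of after-phase patients who could be enrolled only through a nominated consultee, r their composite risk, and 40% the risk of everyone else in both phases. With no true change, the after-phase rate is (1 − a) × 40% + a × r, so the shift is a × (r − 40%). The documents give neither a nor r, and every value below is an assumption.

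| a | r = 40% | r = 55% | r = 65% |
|---|---|---|---|
| 2% | 0 | 0.3 | 0.5 |
| 5% | 0 | 0.75 | 1.25 |
| 8% | 0 | 1.2 | 2.0 |

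The entries are percentage points. For example, 8% × (65% − 40%) = 2.0 points, giving an after-phase rate of 42.0%. A more extreme pair, a = 15% and r = 70%, gives 15% × 30% = 4.5 points. If r is below 40%, the shift is negative.

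**3. Comparison with the right sampling error.** The quantity at risk is a before/after difference, so the 3-point half-width of one group is not the yardstick. The article sets no before-phase sample size. Assuming recruitment in proportion to the 8-week and 20-week phases gives 1000 × 8/20 = 400 at Heartlands and 370 × 8/20 = 148 at Good Hope. Half-width of the difference = 1.96 × √(0.24/n_before + 0.24/n_after):

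- Heartlands: 1.96 × √(0.24/400 + 0.24/1000) = 5.7 points.
- Good Hope: 1.96 × √(0.24/148 + 0.24/370) = 9.3 points.

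A 2-point shift is about a third of the first (2.0/5.7 = 0.35) and a fifth of the second (2.0/9.3 = 0.21). It does not shrink as n grows.

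**The case against.** The case for leaving this alone is substantial. The study is a feasibility pilot, and the article says so directly: "This pilot study is not powered to provide a full comparison of the before and after phases". The after-phase precision calculation is untouched. Even the top of the illustrative range is well inside the sampling error of either contrast. The rule applies at both sites, so some of the shift would show at the control site too. An analysis plan that is not shown may already provide for sensitivity analyses. All of this stands and limits the weight of the point. It does not remove it, because the unequal eligibility is fixed in the article itself, and because the article plans separate contrasts and uses the control-site one to judge success.

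A reader might go further and infer that the added patients are at high risk, so that the after cohorts look worse, a benefit at Heartlands is masked and the control-site criterion is breached. The documents do not support that:

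- No risk is given for patients lacking capacity, with or without a personal consultee.
- Box 1 already removes patients in a terminal phase, typically those with a life expectancy likely to be under 3 months.
- The composite includes stage progression (Outcomes section), which a patient already at stage 3 cannot have. Frailty therefore need not mean a higher composite risk.
- Box 1 also excludes patients who have died by the time of the Outreach intervention. That may act differently by phase and could push the other way.
- A shift of 2 points or less at Good Hope would rarely by itself show up as evidence of change.

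A bias that differs by site is likewise conjecture, since the rule is not site-specific.

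**Conclusion.** The point holds in a limited form. The stated entry rule makes the before and after populations differ, and both planned within-site contrasts, including the control-site check, are open to a case-mix bias. Its size and sign cannot be derived from the documents. It is 0 if the added patients carry the same 40% risk, and up to 2 points if they form as much as 8% of the after-phase cohort with a risk of up to 65%. Those shares and risks are assumptions, as are the before-phase numbers behind the 5.7-point and 9.3-point half-widths. The feasibility aims and the stated confidence intervals are unaffected. The difference is known in advance and cheap to examine, and it bears on the only comparisons that the article offers, so it should be handled openly.

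**What to change.** - For each patient lacking capacity, record the type of consultee and whether a personal consultee was available.
- Prespecify a sensitivity analysis that repeats every before/after contrast, at each site, without the after-phase patients who could be enrolled only through a nominated consultee.
- Describe those patients separately as feasibility information for the planned cluster trial.
- State the phase difference as a limitation beside the recurrent-AKI one in the Data collection and recruitment section.

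Availability matters as well as type. Where either route is allowed, staff may use a nominated consultee for a patient whose relative could have been reached. Dropping everyone enrolled that way would remove patients whom the before-phase rule could have admitted, so the exclusion should be a sensitivity analysis and should not replace the main one.

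The cost is a small addition to the database, a sentence on the sensitivity analysis and a slightly smaller after-phase sample within it. Consent arrangements need not change.
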